**6.2.1.2. Analyses to be performed at PNGIMR Laboratories in Goroka**

1. **DNA extraction and diagnosis of Malaria Infection by Polymerase Chain Reaction (PCR) / Ligase Detection Reaction (LDR)**

DNA extraction will be performed using the QIAmp 96 blood extraction protocol (QIAGEN). This approach enables DNA extraction from 192 samples in 2-3 hours. Using blood samples, it has been used successfully to PCR amplify both human- and malaria parasite-specific amplicons for genotypic and species specific diagnostic assays, respectively. Because DNA extraction methodologies are based upon starting with whole blood, preliminary protease treatment will lyse leukocytes, erythrocytes and Plasmodium parasites. Therefore, purified genomic DNA contains a mixture of human and parasite DNA. The protocol for DNA extraction will be in accordance with the procedures set forth in the Field and Laboratory Procedures Manual.

As each individual’s genomic DNA preparation contains human and parasite DNA, blood samples can be used directly to perform species-specific PCR/LDR-based diagnosis of Plasmodium infection . The protocol for the PCR/LDR-based diagnosis of malaria infection will be in accordance with the procedures set forth in the Field and Laboratory Procedures Manual.

**Typing of Molecular Markers of SP resistance by Polymerase Chain Reaction (PCR) / Ligase Detection Reaction (LDR)**

A random sample of PCR positive infection detected at last treatment time point and delivery will be assess for the presence of know markers of SP resistance in the Pf*dhfr*, *Pfdhps* and *Pvdhfr* genes using established PCR/LDR-based assays.

1. **Diagnosis of sexually transmitted infections by Polymerase Chain Reaction (PCR)**

DNA will be extract directly for self-collected vaginal swabs using established protocol. The thus obtained DNA samples will be assessed for the presence of *N gonorrhoeae*, *C trachomatis* and *T vaginalis* using an established multiplex PCR. The protocol for DNA extraction and PCR-typing will be in accordance with the procedures set forth in the Field and Laboratory Procedures Manual.

1. **Determination of Pneumoccocal Carriage and Drug resistance**

The use of a relatively broad spectrum antibiotic for the prevention of malaria and STIs in pregnancy raised the concern that this intervention may increase resistance in other important bacterial pathogens. As the dose given for malaria control is significantly higher than that recommended for treatment of bacterial illnesses, this is very unlikely. Nevertheless we will assess if IPTp with AZ-SP does increase the risk of antibiotic resistance to AZ, by monitoring resistance levels in pneumococci collect from nasal mucosa for participating women. Pneumococci were selected as carriage rates are high, they are easily collected and cultured.

Per-nasal swab specimens will be cultured and *S. pneumoniae* isolates identified following standard procedures. Resistanceto Azithromycin will be assessedby determination of MICs using strips from AB BioDisk International.Detailed procedures will be set forth in Laboratory Procedures Manual.

### Special Assays or Procedures

All drug used for the study intervention will be procured from manufacturers that can guarantee a GMP quality product and independent quality control of these drugs will be conducted. The Azithromycin will be procured from Pfizer. GMP quality SP and chloroquine has been obtained from Farmamundi, Spain.

### Specimen Collection, Preparation, Handling and Shipping

#### Instructions for Specimen Preparation, Handling, and Storage

1. **Blood Collection**
   1. Finger prick bleeds

At the second and third (where applicable) treatment dose blood samples of approximately 250 μl will be collected from each woman participating in the Protocol. Additional samples will be taken from symptomatic individuals during passive morbidity surveillance. These blood samples will be obtained by the finger prick method.

These samples will provide adequate blood for the preparation of thin/thick blood smears to detect the presence of malaria parasites, type of malaria parasites, and level of parasitemia. A portion of the sample also will be archived in a K+EDTA microtainer for laboratory analyses (e.g. serum & DNA preparation, PCR/LDR-based diagnosis of malaria parasites).

- 1. Venous blood draws

In order to have sufficiently large samples for the detailed immunological measurements detailed in the supplementary protocol, venous blood draws are needed at enrolment and delivery. The volumes of the venous draws are limited to 10 ml. Cell mediated immunology will be studied in separately funded studies.

Drawing venous blood samples will be done by specially trained staff. We will use butterfly needles of 21 gauge and heparinized vacutainers. Residual blood in the tube attached to the butterfly needle will be used to measure haemoglobin levels and make blood smears.

Venepunctures will be performed on veins in the participants’ arms. Upon removal of the needled localized bleeding is efficiently stopped with a small pressure bandage (e.g. a Band Aid). Properly done this procedure is virtually painless. However, if the needle punctures the blood vessel, there is a risk of local bleeding that can result in minor hematoma. In order to assure the safety of participants, they will be monitored following blood draw until it can be ascertained the local bleeding has stopped. Subjects will be instructed to present to the study nurses based at participating health centres in case of localized hematomas or infection at site of needle injection who will then attend to them and if necessary refer them for further treatment.

These samples will provide adequate blood for the preparation of thin/thick blood smears, direct measurement of haemoglobin (enrolment and delivery only), DNA extraction for parasite and host genetic typing as well as provide peripheral blood mononuclear cells (PBMC’s) and parasites for in-depth immunology studies. The sample will be collected in heparinized tubes and separated into red cell, white cell and serum fractions. Samples of these fractions may be stored frozen for later laboratory analyses.

1. **Preparation of Blood Smears**

The preparation of thin and thick blood smears will be in accordance with the procedures set forth in the Field and Laboratory Procedures Manual.

1. **Determining Haemoglobin Concentration**

At enrolment and delivery, haemoglobin concentration will be determined directly in the field by using a HemoCue® device (HemoCue, Ångholm, Sweden) and will be expressed as grams of haemoglobin per decilitre. The instrument records haemoglobin concentrations to the nearest tenth of a gram per decilitre.

#### Specimen Shipment

At regular intervals, blood smears, and blood samples will be transported from the hospital and health centres to the PNGIMR’s Madang laboratories as well as between the Madang and Goroka laboratories. Delivery and receipt of blood smears, and blood samples will be confirmed by both e-mail and telephone and recorded in sample shipment log books. Details for storing and shipping blood smears and blood samples are outlined in the Field and Laboratory Procedures Manual.

DNA aliquots, serum and cryopreserved PBMC and parasites may be shipped to the WEHI or UoM laboratories in Melbourne, Australia, to the Hospital Clinic in Barcelona, or CGHD, Cleveland, Ohio for in-depth laboratory analyses that can not be conducted at the PNGIMR laboratories in Madang or Goroka. This shipment will be done using Air Nuigini freight or specialized dangerous goods couriers. All shipments by air will comply with IATA rules for shipment of diagnostic specimens.

## Randomisation and Blinding

### Randomisation procedures

Women will be randomized to receive SP/AZ or SP/CQ using concealed allocation. Each treatment will be randomly assigned to 4 different treatment codes, resulting in a total of 8 treatment codes (i.e. A, B, C, D, E, F, G, H). A block randomization procedure will be used, with blocks of 32, each containing 4 women assigned to each treatment code. This will help maintain concealment of allocation from study staff to the greatest extent possible.

In order to facilitate field operations independent randomization lists will be produced for each health centre / hospital. The resulting list will contain 1500 women for Modilon Hospital, 500 for each of the peripheral clinics in Madang Town, 500 each for the two field teams operating in the Madang North Coast (Mugil & Alexishafen HC) and 500 for Yagaum Health Centre. .

The lists will be generated by an independent statistician, and the code will be held by the DSMB.

Administration of second and third treatment doses will be placebo controlled.

### Pre-packaging of drugs

Drugs and their respective placebo will be packaged in the PNG IMR into Zip-loc bags. The bags will be marked with the treatment groups A to H.

If the drugs are vomited within 1 hour of administration, replacement drugs will be issued from another bag using the same code.

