The study team Physician or a trained study team Nursing Officer will assess the woman for sign of chronic illness, symptomatic severe anaemia or permanent disabilities that would preclude her participation into the study. (See 5.2 for list of exclusion criteria). If a woman is excluded on health grounds, she will be referred to nearest health facility for treatment.

Every enrolled woman’s health (record) booklet (already owned, or provided at enrolment) will be clearly marked with a study identifier and study ID number. At any study contact, the study team will record all medically relevant data collected during their examination into the health booklet.

Digital photographs will be taken of participating women at enrolment, and a printed version will be kept in a secure file, for tracking of pregnant women who fail to attend appointments, and to ensure accurate identification of women if required

Following assessment the woman will receive the 1st IPTp treatment dose. The drugs will be dispensed in pre-randomised and pre-numbered Ziploc bags that contain all drugs for initial treatment. The first dose (SP and AZ or SP and chloroquine) will be dispensed directly by the study staff. Pack number, date and time of administration will be recorded on the enrolment forms. The tablets will be administered with water. The woman will then be instructed how to take subsequent AZ or chloroquine doses at home. The woman’s treatment allocation will be noted using randomly-generated codes. Treatment allocation will not be revealed to laboratory staff, and will be kept concealed to the maximum extent possible from other study staff (see 6.3.3.). Senior study investigators will be aware of treatment allocation; hence the study will be single blinded.

A thorough physical examination (including axillary temperature, measurement of Hb etc. will only be conducted on enrolled women who spontaneously report as ill to either the study team or the health centre staff. Women with a presumptive diagnosis of malaria will be tested on the spot for malaria infection using a rapid diagnostic test (RDT). If they have a positive RDT they will be treated with a full course of Coartem and their randomised IPTp treatment (drug or placebo) will be delayed for at least 4 weeks. For all women reported sick, detailed symptomatology, results of RDT and treatments given will be recorded on the ‘Morbidity Surveillance Form’.

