### Allocation Concealment and Blinding

The study will be conducted as single blind trial. Second and third treatment doses will be SP and AZ or matching placebo. The treatment allocation codes (i.e. groups A to H) will be held in individual, opaque paper envelopes. The treatment allocation will only be revealed after completion of enrolment by opening the envelope immediately prior to treatment. Only staff directly involved in treatment provision will be provided access the allocation code. Study staff working at other clinical positions, laboratory as well as staff of participating Hospitals and health centres will be kept blinded in regards to the treatment allocation.

The code will be held by the DSMB, principal investigators, study coordinator and staff directly involved in treatment. The code will only be revealed other staff once all women have completed the intervention and have been followed up to delivery, and data has been entered and checked, and data bases are locked. Treatment allocation will be revealed and the effect of SP/AZ on primary and secondary outcome measures will be evaluated. Participants, field and laboratory staff will remain blinded for the entire duration of the study.

In order to assure that treatment allocation is concealed from non-treatment staff as much as possible, staff with access to the treatment codes will sign a confidentiality agreement prohibiting the revelation of the codes to other staff and participants.

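### Fixed group letters on the bags let the open first course reveal the arm to non-dispensing staff who, the protocol says, stay blinded

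*Combined protocol and SAP*

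**What the plan says.** **Codes and lists.** Section 6.3.1 states: "Each treatment will be randomly assigned to 4 different treatment codes, resulting in a total of 8 treatment codes". Randomisation is in blocks, "with blocks of 32, each containing 4 women assigned to each treatment code". To ease field work, "independent randomization lists will be produced for each health centre / hospital". Only one set of eight codes is described; nothing says that the letter-to-arm key is redrawn by site.

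**Bags.** Section 6.3.2 states: "Drugs and their respective placebo will be packaged in the PNG IMR into Zip-loc bags". They carry the group letter ("The bags will be marked with the treatment groups A to H"). After early vomiting, "replacement drugs will be issued from another bag using the same code". Section 6.1.4 describes the bags as numbered in advance and has the pack number recorded at each course. The two sections do not say how number and letter relate, or whether the letter reaches the forms.

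**Contents.** Section 6.1.4 says of course 1: "The first dose (SP and AZ or SP and chloroquine) will be dispensed directly by the study staff". The woman is then told how to take the remaining azithromycin or chloroquine at home. Study Design and section 6.3.1 confine placebo to the later courses.

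**Blinding.** Section 6.3.3 calls the trial single blind. It gives the code to the DSMB, the principal investigators, the coordinator and the staff who give treatment, and keeps it from other clinical, laboratory and facility staff. The safeguards are opaque envelopes, restricted access and a confidentiality agreement. It also states: "Participants, field and laboratory staff will remain blinded for the entire duration of the study".

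**The concern.** A letter shared by many women is a group label. If the contents of any bag with that letter become known, the label gives the arm of everyone who carries it. Course 1 supplies that information, because the arms receive different drugs with no dummy, and the same letter then follows the woman to courses 2 and 3. None of the safeguards in section 6.3.3 stops a person from working out the key in this way, since they protect the code list and not what can be inferred from the bags.

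At stake is the protection of outcomes that depend on staff judgement. A woman who reports illness has a rapid test only if staff make a presumptive diagnosis of malaria (sections 6.1.4 and 6.1.7), and that feeds the incidence of symptomatic malaria. Adverse events are graded by the study clinician (section 9.1), and their attribution to study drug is a secondary outcome. A report that describes all field staff as blinded throughout would claim more than the packaging delivers.

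**Working it through.** **Inputs.** Two arms, four letters per arm, blocks of 32 with four women per letter, and list lengths of 1500 (Modilon) and 500 (each other list), all from section 6.3.1; enrolment of 2792, or 1396 per arm (sections 11.2 and 11.3).

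**1. The plan's own figures.** 2 × 4 = 8 letters; 8 × 4 = 32 women per block. Both reproduce.

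**2. Women per letter.** With one key for the trial, 2792 / 8 = 349 (equally 1396 / 4 = 349). If the key were redrawn by site, which the text does not say, a letter would cover one eighth of that site's list: about 1500 / 8 = 188 places at Modilon and 500 / 8 = 63 elsewhere.

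**3. Latest point at which all letters have appeared.** Seven letters can fill at most 7 × 4 = 28 places, so the eighth appears no later than the 29th woman. One block is 32 / 2792 = 1.1% of enrolment.

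**4. Someone who learns only some course 1 contents.** Assume that the contents of *k* bags become known, drawn at random from one block. The expected number of letters known is 8 × [1 − C(28, *k*) / C(32, *k*)]. The bracket is also the expected share of women whose arm is then known, under a common key.

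| *k* | Bracket | Letters known (expected) |
|---|---|---|
| 1 | 1 − 28/32 = 0.125 | 1.0 |
| 4 | 1 − 20475/35960 = 0.431 | 3.4 |
| 8 | 0.705 | 5.6 |
| 16 | 0.949 | 7.6 |

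**5. Someone who sees every course 1 bag at a site.** In 100,000 simulated blocks all eight letters had been seen after a median of 15 women (95th percentile 22). With knowledge that the letters split 4:4, the key was complete after a median of 9 (mean 9.7, 95th percentile 15). These medians mainly describe the dispenser, who already holds the code. They are a lower limit on the time that other staff would need.

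**6. The blinding claim against the other text.**

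- *Staff who give treatment* hold the code under section 6.3.3 and belong to the field team, yet the same section says that field staff remain blinded.
- *Participants* are said to remain blinded. At course 1 each handles azithromycin or chloroquine and is instructed on that drug. A control woman then moves from chloroquine to azithromycin placebo. She needs no letter to suspect her arm.
- *Other clinical and field staff* are meant to be blinded. They can infer the arm if they see the letter and learn what a course 1 bag with that letter held.
- *Laboratory staff* are meant to be blinded, and nothing shows that they see bags.

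**The case against.** The strongest reply is that the unblinding is declared. Study Design says that those who dispense know the allocation, and section 6.1.4 adds the senior investigators. For the people who routinely handle bags, decoding a letter adds nothing. This stands, and it limits the point to staff outside dispensing. The documents do not show how often such staff see lettered bags. With at least 14 nursing officers (section 6.1.1) and seven field sites (synopsis), an even spread, which is an assumption, gives about two per site, so shared sight of bags is plausible.

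A reader might infer that the matching placebos conceal nothing and that all 2792 × 2 = 5584 later bags are open to anyone who sees them. The documents do not support that. A later bag alone reveals nothing; the viewer must also know the course 1 contents for its letter. The 5584 is an upper bound, because some visits will be missed and women with a positive rapid test at a later visit receive other treatment in place of the scheduled course.

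A reader might also infer that the protocol hides the open first course. It does not: Study Design and section 6.3.1 state which courses use placebo.

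Nor do the consequences reach every outcome. Birth weight is read from a scale. Two microscopists read slides independently (section 11.1.1). Serious and Grade 4 events go to an independent clinician for a causality judgement (section 10.1). Missed visits are followed up by village reporters, who have no described role in dispensing. Tablet appearance is not described either, so the visible difference at course 1 is inferred from the different drugs, the absence of a dummy and the drug-specific instructions.

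Finally, relabelling leaves two other routes open: course 1 itself, and section 6.1.8, where treatment after a positive swab depends on the arm. That is correct. It argues for a more modest blinding claim, but not for keeping the letters.

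**Conclusion.** The point holds in a limited form. Shared letters and an unmatched first course give non-dispensing clinical and field staff an avoidable way to learn the arm. The contents of one course 1 bag disclose the arm of about 349 women under a common key, or of about 63 to 188 list places if the key were redrawn by site. Four letters per arm and blocks of 32 slow this down but do not prevent it.

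Separately, the statement in section 6.3.3 that participants and field staff stay blinded throughout conflicts with that section's own unblinded treatment staff and with the open course 1.

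The outcomes most exposed are symptom-triggered malaria testing and attribution of lower-grade adverse events. The conclusion rests on three assumptions: that course 1 contents can be told apart, that some non-dispensing staff see letters and learn contents, and that the letter key is fixed. The documents support no estimate of the size or direction of bias, and none is offered.

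**What to change.** 1. Keep A to H in the independent statistician's list only. Label course 2, course 3 and replacement bags with unique pack numbers tied to the woman's study ID, so that one woman's course 1 says nothing about another woman's bags. Reconcile section 6.3.2 with the numbered bags of section 6.1.4; if unique numbers already exist, the change is to drop the letter.
2. Amend section 6.3.3 to say that course 1 is open, that participants and treatment staff may know the arm, and that blinding applies to laboratory staff and to clinical and facility staff not involved in dispensing.

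**Cost.** Packing is done in-house and the lists already come from an independent statistician, so this is relabelling plus a pack list. Replacement bags must be matched by number instead of by letter, and the blinding claim becomes more modest. Relabelling does not mask course 1 or the arm-dependent treatment in section 6.1.8, and the amended text should not suggest that it does.

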### Allocation Concealment and Blinding

The study will be conducted as single blind trial. Second and third treatment doses will be SP and AZ or matching placebo. The treatment allocation codes (i.e. groups A to H) will be held in individual, opaque paper envelopes. The treatment allocation will only be revealed after completion of enrolment by opening the envelope immediately prior to treatment. Only staff directly involved in treatment provision will be provided access the allocation code. Study staff working at other clinical positions, laboratory as well as staff of participating Hospitals and health centres will be kept blinded in regards to the treatment allocation.

The code will be held by the DSMB, principal investigators, study coordinator and staff directly involved in treatment. The code will only be revealed other staff once all women have completed the intervention and have been followed up to delivery, and data has been entered and checked, and data bases are locked. Treatment allocation will be revealed and the effect of SP/AZ on primary and secondary outcome measures will be evaluated. Participants, field and laboratory staff will remain blinded for the entire duration of the study.

In order to assure that treatment allocation is concealed from non-treatment staff as much as possible, staff with access to the treatment codes will sign a confidentiality agreement prohibiting the revelation of the codes to other staff and participants.

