The prevalence of carriage of S pneumoniae and of antibiotic resistance will be determined in nasopharyngeal swabs by routine culture and disc diffusion, respectively. Isolates will be stored for further characterization.

1. ***Maternal, perinatal and infant mortality rates.***

The following mortality rates will be determined:

1. Maternal mortality rate (enrolment to 6 weeks post partum). Determined by home visits to communities where mothers lived, and interview of family members and other relevant individuals.
2. Abortion/stillbirth rates. These are defined as death of a fetus before delivery. Abortion is a death before 22 weeks estimated gestation and stillbirth is a death at or after 22 weeks gestation
3. Perinatal mortality rates. These are defined as death (due to any cause) of a child from 22 weeks to 7 days post partum.
4. Infant mortality rate (0-12 months). All cause infant death will be recorded.
5. **Impact of IPTp on development of immunity to malaria in pregnancy**

A detailed description of immunological outcome measures will be given in a separate immunology sub-protocol.

1. **Characteristics of parasites infecting pregnant women.**

A detailed description of parasitological outcome measures will be given in a separate immunology sub-protocol.

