### Secondary Outcome Measures

1. **Prevalence of *P. falciparum* malaria at delivery by microscopy**

This outcome measure will be analysed in women in whom blood films (peripheral and/or placental) are collected at delivery.

1. **Prevalence of *P. falciparum* malaria at delivery by histology**

This outcome measure will be analysed in all women from whom an assessable placental biopsy is collected at delivery.

1. **Maternal Hb at delivery by histology**

This outcome measure will be analysed in all women from whom an Hb measurement at delivery is available.

1. **Incidence of symptomatic malaria**This outcome will be analysed in all women that have had 1 IPTp treatment
2. **Prevalence of STIs on Vaginal swab at 28-34 weeks gestation**

This outcome measure will be analysed in all women in whom an assessable swab is collected at 28-34 weeks. Rates of carriage of N gonorrhoeae, C trachomatis and T vaginalis (assessed by PCR) will be compared between groups.

1. **Maternal, perinatal and infant mortality rates**

All deaths, irrespective of cause of death, occurring in the cohort of pregnant women and their fetuses or children between Enrolment and Final Evaluation Visit (6 weeks post partum for pregnant women, deaths from 22 weeks gestation to 28 days post partum for perinatal mortality, deaths from day 28 of life to 12 months of age for infants) will be considered for this analysis

1. **Reported side effects / Adverse events**

All reported side effects following IPTp treatment, irrespective of total number of treatments a woman received, will be considered for these analyses.

1. **Molecular markers of SP resistance**

This endpoint will be assessed in a random sample of PCR-positive samples collected at 2nd treatment and at delivery.

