## Participant Enrolment and Follow-Up

This study will enrol 2792 pregnant women over a period of 18-24 months. Enrolment and follow up will occur through Hospital and Health Centre Antenatal Clinics. Apart from some ultrasound visits (particularly at enrolment), no additional study visits will be required, beyond visits for standard antenatal care.

Currently there are high levels of ANC attendance in Madang. If women miss a treatment or follow-up visit they will be visited on the next day by a village reporter and encouraged to visit the health centre or the hospital ANC. We therefore expect >90% attendance at any follow-up time point.

However, people in the study areas do occasionally move the village of residence. In addition some people do grow tired of participating in intensive longitudinal follow up studies and withdraw consent for continued participation.

Women that missed more than 2 treatments will be excluded from all analyses except those on drug side effects. Consequently, we expect about 20% loss of follow-up.

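### Code release and outcome evaluation are tied to delivery, but infant mortality runs to 12 months of age and no later lock is defined

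*Combined protocol and SAP*

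**What the plan says.** Section 6.3.3 (Allocation Concealment and Blinding) allows the code to reach other staff only "once all women have completed the intervention and have been followed up to delivery, and data has been entered and checked, and data bases are" in a locked state. The next sentence reads: "Treatment allocation will be revealed and the effect of SP/AZ on primary and secondary outcome measures will be evaluated". No outcome is set aside for a later date.

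Infant mortality is among the secondary outcomes. Section 8.1.2 defines it as "Infant mortality rate (0-12 months). All cause infant death will be recorded". Section 11.1.3 counts "deaths from day 28 of life to 12 months of age for infants". The two windows start at different ages, but both end at 12 months. Section 6.1.6 places the final infant assessment at 12 months of age. Maternal mortality runs to 6 weeks post partum.

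On accrual, section 11.3 states: "This study will enrol 2792 pregnant women over a period of 18-24 months". Sections 5.1 and 6.1 (Participant Database) give 18 months. The synopsis gives a study duration of 48 months.

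On who knows the allocation, section 6.3.3 states: "The code will be held by the DSMB, principal investigators, study coordinator and staff directly involved in treatment". It also states: "Participants, field and laboratory staff will remain blinded for the entire duration of the study".

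Section 15.4 says that entry and review continue throughout the field study, and that data are frozen when entry is complete. Section 11.4.2 gives no method and no censoring rule for any mortality outcome.

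**The concern.** The only milestone that the plan gives for code release and evaluation is built on delivery, and it is followed by evaluation of the secondary outcomes. One of those outcomes cannot be complete until a year after the last delivery. If the team follows section 6.3.3 as written and locks within some months of the last delivery, the youngest infants enter a 0-12 month rate with only part of that period observed.

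Without a censoring rule, those infants stay in the denominator while their later deaths are absent. The reported rate is then too low in both arms, and events are lost from an outcome that has no power calculation in Table 3.

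There is a smaller, related point. Data-entry staff and the database manager (section 15.1) are not clearly within the groups kept blinded to the end. They could therefore learn the allocation while infant follow-up data are still being entered and queried.

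**Working it through.** The plan states no figure for the share of infants under 12 months at the lock, so there is nothing to reproduce.

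**Inputs from the documents**
- Accrual period T: 18 months (sections 5.1 and 6.1) to 24 months (section 11.3).
- Gestation at enrolment: 14-26 weeks (section 4, Study Design).
- Number enrolled: 2792.
- Infant time point: 12 months of age.

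**Assumptions, not in the documents**
- Accrual is uniform; front- and back-loaded accrual are tried as sensitivity checks.
- Delivery is at 39 weeks on average, SD 2.
- The lag L from last delivery to lock is 0 to 12 months.

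**Closed form.** If births are uniform over T months, infants under 12 months at the lock are those born in the last 12 − L months:

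share = (12 − L) / T

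For example, with L = 0 this is 12/18 = 66.7% or 12/24 = 50.0%. With L = 6 it is 6/18 = 33.3% or 6/24 = 25.0%.

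**Simulation.** 400 runs of 2792 women, with entry uniform over T and gestation at entry uniform over 14-26 weeks. The share is lower than the closed form because the spread in gestation at entry thins out the latest births.

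| Lag L (months) | T = 18, simulated | T = 18, closed form | T = 24, simulated | T = 24, closed form |
|---|---|---|---|---|
| 0 | 57.5% | 66.7% | 43.4% | 50.0% |
| 3 | 40.9% | 50.0% | 30.9% | 37.5% |
| 6 | 24.2% | 33.3% | 18.3% | 25.0% |
| 9 | 7.7% | 16.7% | 5.9% | 12.5% |
| 12 | 0% | 0% | 0% | 0% |

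**Accrual shape at L = 0, same gestation at entry.** Front-loaded accrual gives 39.6% (T = 18) and 23.0% (T = 24). Back-loaded accrual gives 81.3% and 67.4%.

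**Follow-up time not yet observed.** An infant under 12 months at the lock lacks on average (12 − L)/2 of its 12 months, so in closed form:

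missing share = (12 − L)/T × (12 − L)/24 = (12 − L)² / (24T)

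- L = 0: 144/432 = 33.3% or 144/576 = 25.0%. A simulation on near-identical assumptions gave 24.8% and 18.8%.
- L = 6: 36/432 = 8.3% or 36/576 = 6.3%.

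The loss of deaths equals these shares only if the death rate is constant over the first year. If deaths cluster early in infancy, fewer are lost.

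**Timing of a complete infant lock.** Enrolment at 14 weeks and delivery at 39 weeks are 25 weeks apart, or about 6 months. The last 12-month visit therefore falls at about 18 + 6 + 12 = month 36 or 24 + 6 + 12 = month 42, before month 48.

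**Other outcomes.** LBW is complete once the 7-day weighing window after the last delivery has closed. The 6-week maternal outcome is incomplete only if the lock falls within 6 weeks of the last delivery.

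**The case against.** The best defence is that section 6.3.3 does not fix a lock date. Delivery is one precondition among several, and data entry, checking and lock must also be finished. Section 15.4 can be read as a single freeze after all field work, including the 12-month visits. Section 11.1.3 says that deaths up to 12 months of age are to be considered, and the 48-month duration leaves room for that.

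Part of this stands. A reader might infer that the databases lock on the day of the last delivery, or that later infant deaths can never be counted. The documents support neither. The lag is unstated, and if it were near 12 months the problem would disappear.

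But the defence does not close the gap. If section 15.4 means one freeze after the last 12-month visit, the delivery milestone in section 6.3.3 has no function and the LBW result waits about a year. If section 15.4 permits a freeze soon after the last delivery, infant mortality is truncated. The sections need reconciling either way.

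A reader might also infer a bias between arms, or a serious loss of blinding. Neither is well supported:
- Randomisation is blocked within each facility (section 6.3.1), so truncation by calendar date should fall about equally on both arms.
- The outcome is death from any cause, which leaves little room for judgement.
- Field staff remain blinded, and the field team conducts the 12-month visit.
- The principal investigators and study coordinator hold the code from the start, so a later release changes nothing for them.

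Finally, the objective is to document mortality rates in each group. No test of infant mortality is planned.

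**Conclusion.** The concern holds as a gap between sections. Code release and evaluation follow a delivery-based lock, infant mortality needs a further year, and no second lock, later evaluation or censoring rule is given.

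Under uniform accrual over 18-24 months, the share of infants under 12 months at the lock would be about 43-67% with no lag, 31-50% at 3 months, 18-33% at 6 months and 6-17% at 9 months. Accrual pattern and lag are assumptions, and accrual shape alone moves the zero-lag figure widely.

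The effect is an understated rate in both arms and fewer events for a descriptive secondary outcome. It would be wrong to extend this to all secondary outcomes: those measured during pregnancy or at delivery are complete by the milestone. The primary LBW comparison is untouched. The plan should be changed, but the trial's main conclusion does not depend on it.

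**What to change.** In section 6.3.3, replace the single milestone with two locks and align section 15.4 with them.

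- **Lock 1**, after the last delivery and its 7-day weighing window: evaluate LBW and the delivery outcomes.
- **Lock 2**, after the last infant's 12-month visit (about month 36-42): evaluate infant mortality.
- **Maternal mortality:** evaluate once 6-week follow-up is complete.
- **Perinatal mortality:** evaluate once its own window has closed. Section 8.1.2 ends that window at 7 days and section 11.1.3 at 28 days, so the definition must be settled first.
- **Any infant mortality result at lock 1:** give it only as a time-to-event estimate censored at the lock date and labelled interim.
- **Access to the code:** staff who do not already hold it and who enter or query infant follow-up data stay without it until lock 2. A wider ban would be more than a wording change. The study coordinator, who cross-checks the CRFs (section 15.1), and the principal investigators, who review the death forms (section 9.3.1), already hold the code.

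The cost is protocol wording and one further database lock, with no added participants or visits. The infant mortality result would come about a year after the primary result, within the 48 months planned.
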